#### Sensitivity analyses

Sensitivity analyses will be restricted to completers only and include a per-protocol analysis. This analysis will include only children from the sleep extension group who complete the study and extend their sleep by at least 30 min per night after 12 weeks. This amount of sleep extension is clinically relevant for outcomes related to body weight regulation and cognitive function (21, 30).

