### Sample size determination

Sample size calculations were designed to achieve 80% statistical power (corresponding to a type II error of 0.2). Two-sided hypothesis testing with a type I error rate of 2.5% (i.e., *P* ≤ 0.025) was chosen because there are two co-primary outcomes, and a 20% dropout rate over 12 weeks was assumed.

A previous study on sleep extension in children aimed for moderate-to-large effect sizes, Cohen's *d* = 0.58, based on preliminary data (21). This study aims to achieve a similar effect size, resulting in an absolute difference in the final BMI z-score of 0.52 units between groups. We consider this effect size to be appropriate and clinically relevant, as studies of lifestyle interventions in children have demonstrated important clinical benefits with decreases in BMI z-score of 0.25–0.50 units (73).

In a previous study of sleep extension in children, including children of any weight status, a mean BMI z-score of 0.9 was reported, with a standard deviation of 0.9 (21). Based on these data, we assume a mean baseline BMI z-score of +1.0. Under these assumptions, we estimate we will need 114 children assigned in a 1:1 ratio between the active and control groups to detect an effect size of d = 0.58. Although sleep intervention studies in children report dropout rates below 4% (21), we based our calculations on a more conservative 20% attrition rate (i.e., five times higher than previously observed but more realistic for our longer study duration and more demanding assessment). We estimated that we would need to enroll 142 children (for 114 completers).

Considering learning and memory, we defined our co-primary outcome as overall 24 h learning. Previous studies on sleep extension in children have found moderate effect sizes for improved performance in the cognitive domain, corresponding to similar effect sizes for the academic performance domain (31). We have not found studies investigating the effects of sleep or sleep extension on 24 h learning effects. In recent experiments, we found that overnight sleep is related to total 24 h skill learning in children and that children benefit from offline learning effects compared to adolescents and young adults (41). Based on the mean performance and standard deviation at baseline among school-aged children aged 8–10 years, we anticipate that a sample size of 142 will allow us to detect a moderate-to-large effect size in the learning and memory domain at *P* ≤ 0.025, with 80% power.

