#### Primary analysis

The effect of the intervention will be evaluated using linear mixed-effects models (LMMs) estimated with restricted maximum likelihood (REML), allowing inclusion of all available observations in the statistical model without imputations.

The LMMs will be performed with fixed effects for group, time, and the group-by-time interaction, with participant included as a random effect. The primary model will include baseline and 12-week measurements. An extended model with 3 time points (baseline, 12 weeks, and 6 months) will be developed to assess the sustainability of effects over the follow-up period. These models will be adjusted for stratification variables and baseline pubertal stage, included as fixed main effects. Model assumptions will be evaluated using residual diagnostics. If model assumptions are not met, appropriate transformations will be considered.

The primary analysis will be conducted using an intention-to-treat approach, including all randomized children according to their group allocation, regardless of whether or not they complete the study.

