Wearing the actigraphy device, polysomnography equipment, and surface electrodes used in EEG and EMG may cause skin irritation. Additionally, in rare cases, EEG-compatible gel may cause an allergic reaction in particularly sensitive individuals. EEG and EMG are safe for use in children. If skin irritation is observed, electrodes and gel are removed, and these measurements are omitted.

MRI is a non-invasive imaging method with no known biological hazards and has been approved for use in children. To minimize distress and motion, children will be acclimatized to the MRI environment using a scanner simulator. Scanning will be terminated immediately if a child shows signs of discomfort or requests to stop.

Finally, to ensure participant safety, vital signs, including resting blood pressure, heart rate, and body temperature, will be assessed at all main visits (A, B, and C). Potential adverse events will be assessed during the study period. If the child's general condition precludes continuing the study, as determined by the study personnel or the medical expert, participation will be discontinued. Participation will also be discontinued in cases of significant non-compliance, lack of cooperation, or unforeseen events that make the child ineligible to participate. Additionally, all participants are insured in accordance with national legal requirements in the event of injury resulting from study procedures.

Regardless of the outcome, the results of the study will be published in peer-reviewed journals and presented at scientific conferences.

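### The sensitivity analyses are limited to completers and a per-protocol subset, so they cannot test the result against dropout linked to non-adherence

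*Protocol article*

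**What the plan says.** Under Primary analysis, the article specifies a REML linear mixed model with group, time and their interaction, "allowing inclusion of all available observations in the statistical model without imputations". It follows intention to treat, "including all randomized children according to their group allocation, regardless of whether or not they complete the study". On time points it says: "The primary model will include baseline and 12-week measurements".

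Under Sensitivity analyses it says: "Sensitivity analyses will be restricted to completers only and include a per-protocol analysis". The per-protocol set keeps only "children from the sleep extension group who complete the study and extend their sleep by at least 30 min per night after 12 weeks".

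Four other places bear on the point:

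- Sample size determination: "a 20% dropout rate over 12 weeks was assumed". The same section calls this conservative, because earlier sleep intervention studies in children lost under 4%.
- Ethics and dissemination: "Participation will also be discontinued in cases of significant non-compliance, lack of cooperation, or unforeseen events that make the child ineligible to participate".
- Randomization and blinding: children and parents cannot be blinded. Under Interventions, only the extension arm is asked to change bedtimes.
- Data collection and outcomes: children who stop the intervention or withdraw are invited to an early termination visit. For withdrawal in the active phase it matches Visit B.

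**The concern.** A sensitivity analysis should vary the assumption on which the primary result most depends. Here that assumption is that, given the observed data, children without a week-12 value would have resembled those who have one. The two stated analyses do not relax it. One drops the incomplete children. The other also drops extension-arm children who gained too little sleep. If children who did not adhere, and so did not benefit, are also those lost, the primary estimate is too favourable. The completers-only estimate would be too favourable by about the same amount, and the per-protocol estimate by more. Agreement between them could then be taken as robustness when it is not.

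**Working it through.** **1. The plan's own figure.** Inputs from Sample size determination: d = 0.58 (0.52 BMI z-score units, SD 0.9), two-sided alpha 0.025, power 80%, 1:1 allocation. n per arm = 2(2.241 + 0.842)²/0.58² = 56.5, so 57 per arm and 114 in total, as stated. 114/0.8 = 142.5, against 142 stated.

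**2. Does a completers-only analysis assume more?** Large-sample simulation of 400,000 children with a simplified random-intercept model without covariates. Assumptions: SD 0.9, r = 0.5, 0.7 or 0.9, true effect −0.52. Extension-arm dropout depends on baseline BMI z-score (35% above 1, 5% otherwise); control dropout is 20% at random. The data are therefore missing at random.

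| r | Mixed model | Completers only |
|---|---|---|
| 0.5 | −0.521 | −0.455 |
| 0.7 | −0.517 | −0.476 |
| 0.9 | −0.519 | −0.506 |

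The mixed model recovers the truth. The completers-only estimate is off by an amount that shrinks as r rises.

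**3. Can the stated analyses reveal adherence-linked dropout?** Same set-up, but assume that 30% of the extension arm do not adhere and gain nothing, and that all its dropout (20% of the arm) comes from them. True intention-to-treat effect: −0.52 × 0.70 = −0.364. Of the 80% who remain, 70/80 adhered, so the expected completers' effect is −0.52 × 0.875 = −0.455.

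| r | Mixed model | Completers only | Per-protocol vs control completers |
|---|---|---|---|
| 0.5 | −0.455 | −0.455 | −0.520 |
| 0.7 | −0.451 | −0.450 | −0.514 |
| 0.9 | −0.453 | −0.453 | −0.519 |

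Completers-only repeats the biased primary estimate. Per-protocol lies further from −0.364.

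**4. How large a departure would matter?** The planned contrast is a difference in change, with SD of change = 0.9 × √(2(1 − r)). The article gives no r, so a range is shown. Threshold = t(0.9875; 112 df) × SD of change × √(2/57), with t = 2.272. If a fraction f of the extension arm is missing, tipping shift = (observed difference − threshold)/f.

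| r | SD of change | Threshold | Shift for 0.42, f = 20% | Shift for 0.52, f = 20% | Shift for 0.42, f = 4% | Shift for 0.52, f = 4% |
|---|---|---|---|---|---|---|
| 0.5 | 0.900 | 0.383 | 0.18 | 0.68 | 0.92 | 3.42 |
| 0.7 | 0.697 | 0.297 | 0.62 | 1.12 | 3.08 | 5.58 |
| 0.9 | 0.402 | 0.171 | 1.24 | 1.74 | 6.22 | 8.72 |

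Shifts are in BMI z-score units. The threshold is held at 57 per arm throughout. Imputation variance is ignored, which overstates the shifts somewhat. At 4% missing, more than 57 per arm would remain, which works the other way.

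**5. Dilution if the missing children gained nothing.** At 20% missing, 0.52 × 0.80 = 0.416, still above 0.383. At 4%, 0.52 × 0.96 = 0.499. At 30%, beyond the planned attrition, 0.52 × 0.70 = 0.364, which is below the threshold only at r = 0.5.

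**The case against.** The strongest reply is that this is an omission which a fuller analysis plan could fill, and that the article never claims its sensitivity analyses test the missing-data assumption. That is partly fair: the only rationale given concerns the 30-minute cut-off. But the section labels these the sensitivity analyses and limits them to completers. A fuller plan that added one on all randomised children would depart from that sentence, so the wording needs changing in either case.

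Three further points stand and limit the concern:

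- Early termination visits may recover outcome data from children who stop. They are by invitation, and they do not test the assumption for those who stay away.
- The 20% attrition is deliberately conservative. Near 4%, the concern has little numerical weight.
- At high r, completers-only and the mixed model differ little (0.013 at r = 0.9 in step 2). What then remains is that neither departs from missing at random.

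A reader might infer from "Participation will also be discontinued in cases of significant non-compliance" that informative dropout in the extension arm is likely. The documents do not support that. The rule is undefined, is not confined to one arm, and is not said to end outcome collection. The Compliance section defines compliance by sleep gained after 12 weeks, so failing that definition is known only around Visit B.

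A reader might also take 0.18 z to mean that a positive result would be fragile. That figure needs r = 0.5 and an observed difference only just above the threshold.

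**Conclusion.** The concern holds in limited form. As stated, the sensitivity analyses need an equal or stronger missing-data assumption than the primary model, or select on a post-randomisation variable. They cannot show robustness to adherence-linked dropout. That follows from the method and does not depend on the illustrative numbers. In the simulation the direction was the same at every correlation tried.

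The size is uncertain. At the planned 20% attrition and the planned effect, even complete loss of benefit among the missing leaves the difference above the threshold. The tipping shift ranges from 0.18 to 1.74 z over the values tried, and is about five times larger at 4% missing. These figures assume SD 0.9 at both time points and concern BMI z-score only. The article gives no numerical inputs for the same calculation on learning ability.

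It would go too far to say that the primary analysis is invalid or that a positive result would probably be overturned. The primary analysis stands, but the check on it should be changed.

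**What to change.** Reword the Sensitivity analyses section, and the analysis plan to match:

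- Label the completers-only and per-protocol analyses supplementary.
- For both co-primary outcomes, make the sensitivity analysis a delta-adjusted (tipping-point) multiple imputation on all randomised children, using any early termination data. Shift the imputed week-12 values in the extension arm in the unfavourable direction, and report the shift at which the conclusion changes.
- Add one control-based imputation, in which missing extension-arm children are imputed from the control arm.
- Fix the range of shifts before unblinding, and report the number missing by arm and reason.

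The cost is revised wording and a few hours of programming. No new data are needed, and the primary analysis, sample size and trial conduct are unchanged.

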#### Exploratory analyses

In an exploratory analysis, interaction terms between group allocation and sex and between group allocation and BMI status will be included in the linear mixed models. Additionally, correlation and regression analyses will be used to evaluate the continuous association between changes in sleep duration and the outcomes.

Two-sided *P*-values ≤ 0.025 will be considered statistically significant for the primary outcomes. For secondary and exploratory outcomes, *P*-values ≤ 0.05 will be considered statistically significant. Statistical analyses will be conducted using IBM SPSS Statistics and R.

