## Abstract

**Background:**

Sleep is essential for children's health, cognitive development, academic performance, and overall well-being. Short sleep duration has been associated with several adverse outcomes, including an increased risk of obesity and impaired cognitive functions. Despite these associations, few studies have demonstrated causal links with these outcomes. Objective: To assess the effects of sleep extension on body weight regulation and learning ability in school-aged children with nocturnal sleep below recommendations for their age. Method: More2Sleep is a randomized, controlled, parallel trial involving 142 school-aged children (6–12 years old) who are “short-sleepers” (≤9 h/night). The children will be randomly assigned to a sleep extension group (by ∼45 min/night, achieved by going to bed 60–90 min earlier than usual; *n* = 71) or a control group (habitual sleep schedule; *n* = 71) guided by a family advisor for 12 weeks, followed by a 6-month inactive follow-up. All outcomes will be measured at baseline and 12 weeks. Selected outcomes will be reassessed at the 6-month follow-up to evaluate the sustainability of the intervention. Subgroups of children will undergo additional tests (substudy-I: metabolism and appetite; substudy-II: structural, functional, and diffusion MRI) to evaluate the mechanisms by which sleep may affect weight homeostasis and cognitive functions. Co-primary outcomes include the change in BMI z-score and learning ability from baseline to 12 weeks. Secondary outcomes include percent body fat, dietary energy intake, hunger and satiety, physical activity, energy expenditure, brain activity patterns, and cognitive and academic performance. Discussion: This study has broad implications as it can potentially inform future sleep recommendations and treatment strategies to reduce overweight/obesity and improve children's metabolic health and learning abilities.

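### Effect modification by sex and BMI status is written as two-way group terms; in a model whose intervention effect is group-by-time, these do not test whether that effect differs

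*Protocol article*

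**What the plan says.** Under Primary analysis, the protocol article defines mixed models with "fixed effects for group, time, and the group-by-time interaction, with participant included as a random effect". It adds that "The primary model will include baseline and 12-week measurements", so baseline is an outcome row and not a covariate. A further version covers three visits: "An extended model with 3 time points (baseline, 12 weeks, and 6 months) will be developed". The models are "adjusted for stratification variables and baseline pubertal stage, included as fixed main effects". Sex is one of the stratification variables (Randomization and blinding), so it enters as a main effect only.

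The Abstract puts the primary comparison on the change scale: "Co-primary outcomes include the change in BMI z-score and learning ability from baseline to 12 weeks". In these models, that comparison is the group-by-time coefficient.

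Under Exploratory analyses, effect modification is described in one sentence: "interaction terms between group allocation and sex and between group allocation and BMI status will be included in the linear mixed models". No term that combines time with sex or with BMI status is named anywhere in the article.

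**The concern.** If group-by-time is the intervention effect, then asking whether the effect differs by sex means asking whether group-by-time differs by sex. That is a three-way term. A model with group, time, group-by-time, sex and group-by-sex forces the group-by-time effect to be the same in boys and girls, so it cannot express the hypothesis. The group-by-sex coefficient instead describes an arm difference pooled over visits, one of which precedes randomisation.

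Two things are at stake. A real difference in benefit has little chance of being detected, and a null result from so weak a test could be read as evidence of a uniform effect. The reported estimate would also be the wrong size. The question is a natural one for BMI status, because the Eligibility criteria set no weight limit and one co-primary outcome is BMI z-score.

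**Working it through.** **Inputs from the article (Sample size determination).** SD of BMI z-score 0.9; target effect d = 0.58, or 0.52 units; 114 completers at 1:1; two-sided alpha 0.025; power 80%. Exploratory outcomes use 0.05 (Exploratory analyses).

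**Assumptions, not in the article.** Within-child correlation r between baseline and 12 weeks, taken as 0.7 to 0.95; equal variances at both visits; sexes balanced within arm, giving four cells of 114/4 = 28.5; complete data; a true sex difference in the 12-week effect of δ = 0.30.

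**The plan's own figure.** n per arm = 2(z₀.₉₈₇₅ + z₀.₈)²/d² = 2(2.241 + 0.842)²/0.58² = 56.5, rounded up to 57, or 114 in all. This matches the article. The present point does not depend on that calculation; it only borrows the SD and the 114.

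**What each term estimates (balanced, complete, two visits).**

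- Two-way group-by-sex: the contrast of child means over the two visits. The true modification is 0 at baseline and δ at 12 weeks, so the expected value is (0 + δ)/2 = δ/2. The variance of a child's two-visit mean is σ²(1 + r)/2.
- Three-way group-by-time-by-sex: the contrast of child changes. The expected value is δ. The variance of a change is 2σ²(1 − r).
- In the three-visit model, a modification that is constant after baseline gives the two-way term an expected value of (0 + δ + δ)/3 = two thirds of δ.

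**Standard errors.** A difference of differences over four cells of 28.5 gives:

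- SE(two-way) = √[4 × 0.81 × (1 + r)/2 ÷ 28.5]
- SE(three-way) = √[4 × 0.81 × 2(1 − r) ÷ 28.5]

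**Power at two-sided 0.05 (normal approximation), δ = 0.30.** The two-way term has expectation 0.15.

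| r | SE two-way | power two-way | SE three-way | power three-way |
|---|---|---|---|---|
| 0.70 | 0.311 | 7.7% | 0.261 | 21% |
| 0.80 | 0.320 | 7.6% | 0.213 | 29% |
| 0.90 | 0.329 | 7.4% | 0.151 | 51% |
| 0.95 | 0.333 | 7.4% | 0.107 | 80% |

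The ratio of expected test statistics, three-way over two-way, is √[(1 + r)/(1 − r)]: 2.4 at r = 0.7 and 6.2 at r = 0.95.

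**Simulation check.** 20,000 simulated trials per scenario, using these contrasts, with no effect in one sex and −0.52 in the other:

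- The two-way term averaged about −0.26, with power 12 to 14% for r = 0.7 to 0.9.
- The three-way term averaged about −0.52, with power 51%, 68% and 93% at r = 0.7, 0.8 and 0.9.
- With no effect in either sex, both terms rejected in about 5% of runs.

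**Baseline imbalance.** With the same effect of −0.26 in both sexes and a stable group-by-sex gap of 0.5 planted at baseline, the two-way term averaged about +0.50 and rejected in 32 to 36% of runs. The three-way term stayed near 0 and rejected in about 5%. The 0.5 is illustrative. It shows what a given imbalance does to the estimate and is not an error rate over randomisations.

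**The case against.** **The sentence may be shorthand.** It names factors, does not say that time is excluded, and refers back to models already built around group-by-time. An article may leave exact exploratory model terms to a fuller document. This reading is possible, and it is why the point is limited to the literal text. But the article writes group-by-time when it means time to be involved, and here it writes only group allocation. An analyst who codes what is printed fits the wrong term.

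**The size depends on r.** This is right. At r = 0.7 or 0.8 even the correct term would usually miss a 0.30 difference, so part of the low power is a sample-size limit. The gain also need not carry over to learning ability, which is itself a 24-hour difference score and has no between-visit correlation in the article. At r = 0.3 the ratio above is only 1.36, and at r = 0 there is no gain.

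**False positives.** A reader might infer that chance baseline imbalance would inflate false claims of effect modification. The design does not support that: under randomisation the two-way term keeps its nominal 5% level. What remains is that, in the one trial run, any observed imbalance goes straight into the estimate.

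**The analysis is exploratory.** This is also right. No primary estimate, test or sample size depends on it.

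**Conclusion.** The point holds for the terms as printed. They target half the modification in the two-visit model (two thirds of a constant one in the three-visit model) and are tested against between-child variance. For a 0.30 difference in BMI z-score effect, power is 7 to 8% as written, against 21 to 80% with the three-way term over the assumed r of 0.7 to 0.95. The direction is the same at every r in that range; the size is not fixed by the article. A reader might take the top of the range as the expected gain, but nothing in the article supports r = 0.95 over a lower value. For learning ability the gain is unknown and would be smaller if its between-visit correlation is lower. The defect is confined to the exploratory subgroup results. It should be corrected because a stated term tests the wrong quantity and the correction is nearly free.

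**What to change.** In Exploratory analyses, replace the two-way terms with group-by-time-by-sex and group-by-time-by-baseline-BMI-status, each with all lower-order terms (including modifier-by-time and group-by-modifier). State that BMI status is taken at baseline. Name the 12-week three-way contrast as the test of effect modification, and report the 12-week group-by-time estimate with its interval within each subgroup.

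A group-by-modifier term in a baseline-adjusted model of the 12-week value is an acceptable alternative. It is a different estimator, not an equivalent one, and it omits children without a 12-week value, whereas the planned models use all available observations.

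The cost is one sentence in the plan and one line of code. No new data are needed, and nothing changes in the primary analysis.

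### Testing each primary outcome at a fixed 0.025 is valid, but Holm's procedure is more powerful at the same implied 5% family-wise error

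*Protocol article*

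**What the plan says.** The abstract names two primary outcomes: "Co-primary outcomes include the change in BMI z-score and learning ability from baseline to 12 weeks".

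The section Sample size determination states "Two-sided hypothesis testing with a type I error rate of 2.5" per cent and says that this level "was chosen because there are two co-primary outcomes". The trial is sized on it for 80% power and d = 0.58, giving 114 completers and 142 enrolled.

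The closing paragraph of Statistical analysis (under Exploratory analyses) repeats the level as the decision rule: two-sided P values at or below 0.025 "will be considered statistically significant for the primary outcomes".

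The article describes no step-down, hierarchical or alpha-recycling rule, and it does not require both outcomes to be significant. It does not state a family-wise level; 5% is inferred from 2 × 0.025.

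On the learning outcome, the section Learning ability describes both a motor skill task and a word memory test. Sample size determination names overall 24 h learning as the co-primary outcome, and Learning ability defines that quantity on the motor task.

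**The concern.** Under the fixed rule, the second outcome is held to 0.025 even after the first has succeeded. A P value between 0.025 and 0.05 is then called non-significant, although a 5% family-wise target does not require it. Holm's procedure holds the same family-wise level under any dependence between the tests and rejects at least whatever the fixed rule rejects.

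This matters most when both outcomes respond, which is what the Discussion expects. The Discussion also concedes that the study period may be too short to show changes in either outcome, so power that costs no extra children is worth having.

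**Working it through.** **Inputs from Sample size determination.** Two-sided alpha of 0.025 per outcome; 80% power; d = 0.58, consistent with the stated difference of 0.52 and SD of 0.9 (0.52 / 0.9 = 0.578); 114 completers at 1:1, so n = 57 per arm; 20% dropout.

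**Assumptions.** The article gives no number for the learning effect beyond moderate-to-large, so d = 0.58, 0.30 and 0 are used. It gives no correlation between the two test statistics, so 0, 0.3 and 0.5 are used.

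**Step 1: reproduce the plan's figure.** The normal-approximation formula is n per arm = 2(z₁₋α/₂ + z₁₋β)² / d². With z = 2.241 (alpha 0.025, two-sided) and 0.842, this is 2 × 3.083² / 0.58² = 56.5, so 57 per arm and 114 in total, as stated. Enrolment is 114 / 0.8 = 142.5, against 142 stated. The design therefore rests on the fixed 0.025 level.

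**Step 2: power of a single test at 57 per arm** (noncentral t, 112 df, noncentrality d√(57/2)).
- d = 0.58: 0.794 at alpha 0.025 and 0.866 at alpha 0.05.
- d = 0.30: 0.255 at alpha 0.025 and 0.355 at alpha 0.05.

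**Step 3: closed form at correlation 0.** Write p for power at 0.025 and q for power at 0.05. For two outcomes with the same effect:
- Both significant, fixed rule: p² = 0.794² = 0.630.
- Both significant, Holm: 2pq − p² = 2 × 0.794 × 0.866 − 0.630 = 0.745.
- Per outcome, Holm: p + p(q − p) = 0.794 + 0.794 × 0.0725 = 0.851.

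For unequal effects, an outcome's Holm power is its own p plus the other outcome's p times its own (q − p). The weaker outcome at d = 0.30 beside d = 0.58 has 0.255 + 0.794 × 0.0997 = 0.335.

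**Step 4: simulation at correlations 0 to 0.5** (2,000,000 pairs of t statistics per scenario).

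| Effects (d) | Quantity | Fixed 0.025 | Holm |
|---|---|---|---|
| 0.58 and 0.58 | both significant | 0.63–0.68 | 0.75–0.77 |
| 0.58 and 0.58 | each outcome | 0.79 | 0.84–0.85 |
| 0.58 and 0.58 | at least one | 0.96–0.91 | 0.96–0.91 |
| 0.58 and 0.30 | weaker outcome | 0.26 | 0.33–0.34 |
| 0.30 and 0.30 | each outcome | 0.26 | 0.28–0.29 |
| 0.30 and 0.30 | both significant | 0.07–0.12 | 0.12–0.19 |
| 0.58 and 0 | non-null outcome | 0.794 | 0.795–0.796 |
| 0.58 and 0 | null outcome rejected | 0.025 | 0.042–0.045 |
| 0 and 0 | any false rejection | 0.047–0.049 | 0.047–0.049 |

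A normal approximation gives values about one point higher and the same gains.

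**Step 5: dependence on the size of the family.** Suppose word recall were also tested as primary and either learning score could carry the claim. With BMI z-score at d = 0.58, both learning scores null, correlation 0 to 0.5 between them and independence from BMI z-score, a false learning claim occurs in about 4.7–4.9% of trials under the fixed rule. Under a two-test Holm rule applied loosely to the three scores it occurs in about 8.2–8.7%, and under a proper three-test Holm (0.05/3, then 0.025, then 0.05) in about 4.3–4.5%.

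**The case against.** The strongest reply is that nothing here is wrong. The 0.025 level is pre-specified, the same in design and analysis, and gives about the planned 80% power per outcome. That stands: this is a point of efficiency, not validity. A reader might infer that the fixed rule inflates error, leaves the trial short of its stated power or calls for a new sample size. The documents support none of these, since the 114 reproduces at the stated level.

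A reader might also take Holm as a gain with no downside. That goes too far. The article states a 2.5% error rate, and 5% across the family is an inference. When the other outcome truly works, a null outcome's own error rises from 2.5% to about 4.5%, within 5% family-wise but looser than 2.5%. Fixed 0.025 tests also pair directly with 97.5% confidence intervals, whereas Holm has no equally simple match.

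The size of the gain depends on the effects. The figures at d = 0.58 on both outcomes are the favourable case; at d = 0.30 on both, power per outcome rises by only about three points.

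Finally, two-test Holm is safe only if the family has exactly two tests. Because the word memory test is also described under the primary outcome, a reader might infer three. Read together, Sample size determination and the definition of 24 h learning point to the motor score alone. If word recall were primary as well, two-test Holm would not hold 5%, and neither would a bound built on two tests at 0.025 (3 × 0.025 = 7.5%).

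**Conclusion.** The fixed rule is valid but less powerful than Holm at the same implied family-wise error. That ordering needs no assumption about effect size or correlation; the size of the gain does. With 57 per arm, it is about 10 to 12 points in the chance of both outcomes succeeding and 5 to 6 points per outcome when both effects are d = 0.58. For an outcome at d = 0.30 beside one at 0.58 it is about 8 to 9 points, and it is almost nothing for the other outcome when one effect is null. The chance of at least one success is the same under both rules. The conclusion rests on a 5% family-wise target and on a single learning test in the primary family. It is a worthwhile, inexpensive improvement and not the correction of an error.

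**What to change.** Before unblinding, replace the fixed threshold with this rule: compare the smaller of the two primary P values with 0.025 and, if it is significant, compare the other with 0.05. State the 5% family-wise level explicitly. In the same sentence, name overall 24 h learning on the motor task as the only learning test in the primary family. If word recall is also to be primary, use three-test Holm: 0.05/3, then 0.025, then 0.05.

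Keep 114 completers and 142 enrolled as the conservative planning basis, and report 97.5% confidence intervals alongside the Holm decisions.

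The cost is a short change of text, plus an amendment to the ethics committee and the registry entry, as Ethics and dissemination provides. No further children, visits or data are needed.
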